### Analyses plans

For the primary outcome, the analysis will contrast mortality at 28 days among preterm infants between the intervention and control groups. This will be performed using hierarchical, targeted maximum-likelihood estimation which accounts for within-cluster correlation by controlling for cluster-level covariates [23]. The baseline covariates we will measure for each facility include delivery volume, baseline neonatal mortality rate among preterm infants, preterm birth rate, and country. Additionally, targeted maximum-likelihood estimation will allow us to incorporate individual-level baseline covariate information (such as date of presentation, maternal age, parity/gravidity, HIV status, maternal and fetal complications at presentation, last menstrual period (LMP), infant birthweight, final diagnosis of newborn) in order to improve precision. We will directly incorporate knowledge of the pair-matched randomization scheme into estimation by making the targeting stage of this procedure a function of this known assignment mechanism. Primary outcome data analysis will be conducted in collaboration among in-country partners and UCSF.

Secondary analyses will also be performed, in some cases contrasting secondary outcomes between the intervention and control groups, and in others contrasting these outcomes pre and post intervention within the intervention groups. Secondary analyses will primarily be descriptive, comparing means or proportions between groups, trends over time, composite scores as appropriate for each measure. Both primary and secondary analyses will be conducted in R or Stata. Process data including qualitative interviews or reports will be analyzed by hand or in Atlas ti, identifying and grouping themes that emerge.

Additional analyses will be conducted for each intervention component. For example, PRONTO-related knowledge will be assessed against the standard guidelines for management. Simulation and debrief videos will be analyzed using Studiocode™ software which enables the systematic coding of videos to measure of changes in use of EBPs, as well as teamwork and communication techniques. Video analysis of simulation and debrief results will be shared with participants in the form of structured feedback to PRONTO mentors on their simulation and debriefing facilitation skills.

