### Study population

In all facilities, women accessing delivery care services who are admitted for labor will be eligible for this study. Anonymized data on all deliveries will be extracted from maternity registers. For follow-up, mothers of newborns who are discharged alive and born less than 2500 g or between 2501 g and 3000 g while also being identified as less than 37 weeks by recorded GA in the maternity register are being asked to participate in this study and approached for consent for follow-up for 28-day outcome. These inclusion parameters were selected based on baseline data showing a poor correlation between birthweight and reported GA in the maternity register. Women or newborns from enrolled sites who are referred to one of the three referral facilities will remain in the study. Their outcomes will be allocated to the facility to which the woman first presented.

Healthcare workers providing labor and delivery and immediate newborn care services at referral, control, and intervention facilities will participate in DS initial and refresher workshops, DQAs, as well as initial instruction and minimal refreshers or reorientation on use of the mSCC. Intervention sites will have ongoing support for mSCC utilization, in addition to the other reinforcing intervention components, PRONTO and QI. Healthcare providers in intervention facilities who provide consent for PRONTO simulation trainings will also be enrolled as study participants to ascertain changes in knowledge and practices. Facility staff in the intervention facilities will be organized into QI teams to develop and implement QI programs.

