#### PRONTO simulation-based training

The Kenya-Uganda unified PRONTO emergency obstetric and neonatal care simulation training will emphasize the identification, triage, and management of preterm labor and birth with a curriculum specifically adapted for this context. It will include strengthening preterm labor identification with more accurate GA assessments, intrapartum care, and immediate management of fragile infants. The training also emphasizes identification and management of preeclampsia, chorioamnionitis, and other conditions related to preterm birth. The mSCC will be integrated into all PRONTO clinical activities to provide facility staff with continued opportunities to reinforce its use. Any change ideas that arise from these PRONTO activities will be integrated into QI efforts.

Selection of PRONTO mentors/trainers will be conducted in each country, with an initial pool of up to 15 candidates from which we will select the 5–10 highest performing trainers. Due to the overlapping clinical and curricular content between the two countries, refreshers will be conducted as joint facilitator training for the Kenyan mentors and Ugandan trainers. However, the training mode of delivery will vary between Kenya and Uganda. Kenya will utilize an in situ mentoring program whereby each intervention facility will receive high-intensity/4-day per week mentorship and a pair of mentors will rotate among intervention sites during the study duration. They will spend a combined total of 9–12 weeks at each intervention facility over the study duration and visits will include bedside mentoring, video-recorded, in situ simulations, knowledge reviews, skills stations, teamwork activities, and mSCC support. In Uganda, a high-intensity/shorter modular strategy will be used. A modular-based training program will be paired with 2-day-long in-situ simulation refresher and training visits. Modules and refresher/training visits will be spread out during the study period, and will similarly amount to approximately 6 weeks of mentorship. Thus, while the mode of delivery for training in each country will be different, provider teams in each country will receive approximately 56–58 h of PRONTO-based instruction using the same curriculum.

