### Intervention roll-out

The approach for roll-out of the intervention package will be as follows:*Baseline*: Across all selected facilities, preliminary DS with initial introduction of the mSCC will allow us to conduct a baseline survey to measure incidence of preterm births and preterm mortality in all facilities (at least 2 months). Baseline data will also be collected on key variables that are predictive/correlated with the primary outcome of mortality rate among preterm infants, including but not limited to number of deliveries, number of low birthweight babies, number of neonatal deaths, number of stillbirths, presence of a newborn corner, personnel capacity for intrapartum/postnatal care, etc.*Step 1*: Facilities will be pair-matched using key factors correlated with outcomes. Specifically, sites will be pair-matched based on variables collected during baseline that are predictive or correlated with the primary outcome of mortality rate among preterm neonates (i.e., delivery volume, number, and type of providers, facility-based neonatal mortality rate).*Step 2*: Within each matched pair, one facility will be randomized to the intervention arm and the other will be randomized to the control arm. Intervention facilities will receive PRONTO and QI interventions in addition to DS and mSCC. Randomization and allocation will be done using a computerized random number generator by the statistical team with no contact or direct interest in any specific facilities. As this is a cluster trial, there will be no blinding or allocation concealment.*Step 3*: Upon accruing sample size, the control arm facilities will be assigned to the full intervention, adding PRONTO training and QI cycles.

Figure 2 depicts the schedule of enrollment, interventions, and assessments to be conducted.

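### Complications at presentation are offered as an individual baseline covariate for the primary TMLE, but they are recorded after facility randomisation and the package may change how they are recorded, so adjusting for them can bias the mortality contrast in either direction

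*Protocol article*

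**What the plan says.** Under Analyses plans, the protocol article describes a hierarchical targeted maximum-likelihood analysis of 28-day mortality. Besides facility-level covariates, the method is to allow use of "individual-level baseline covariate information (such as date of presentation, maternal age, parity/gravidity, HIV status, maternal and fetal complications at presentation" and further items: last menstrual period, birthweight and "final diagnosis of newborn) in order to improve precision". The entry at issue, with the item that follows it, reads "maternal and fetal complications at presentation, last menstrual period (LMP"). Precision is the only stated purpose. The pair-matched randomisation is to be used by "making the targeting stage of this procedure a function of this known assignment mechanism".

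Under Intervention roll-out, randomisation follows the baseline period and the matching: "Within each matched pair, one facility will be randomized to the intervention arm and the other will be randomized to the control arm". The same section says that there is no blinding, and defines the contrast: "Intervention facilities will receive PRONTO and QI interventions in addition to DS and mSCC". Controls receive PRONTO and QI only once the sample size has been reached.

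Under PRONTO simulation-based training: "The training also emphasizes identification and management of preeclampsia, chorioamnionitis, and other conditions related to preterm birth". Under Study population: "Intervention sites will have ongoing support for mSCC utilization, in addition to the other reinforcing intervention components, PRONTO and QI"; otherwise staff receive initial checklist instruction and minimal refreshers. Under Data collection/quality control, facility care providers make the register entries. Under Modified Safe Childbirth Checklist, the checklist, with its prompts on risk factors and history, goes into every woman's record in both arms.

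**The concern.** Covariate adjustment in a randomised trial is safe when the covariate cannot depend on the assigned arm. This item is called baseline, and the words about presentation make it sound pre-treatment. In a cluster trial, however, the relevant time point is the randomisation of the facility, and these women arrive after it. A complication may truly predate care, but its record depends on staff whom one arm trains to look for it.

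If the same woman is more likely to be recorded as complicated in one arm, women with the same recorded value are not comparable between arms. The unadjusted contrast would be free of this problem, so the adjustment itself would introduce the bias, in the primary analysis of mortality. The document states no safeguard, such as ascertainment independent of arm or a rule limiting covariates to those the package cannot affect.

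**Working it through.** The plan gives no figure on this point, so there is none to reproduce. The check asks what adjustment does when the package has no effect and only the recording differs.

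**Inputs**
- Mortality 25% in both arms: the no-intervention figure under Sample size and power calculations, with no true effect imposed.
- Assumed, not in the document: 30% of women truly complicated; mortality 40% if complicated; no false positives; a proportion *d* of true complications recorded.
- Mortality if not complicated follows: (0.25 − 0.30 × 0.40)/0.70 = 0.1857.

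**Formulae**
- Recorded prevalence = 0.30*d*.
- Mortality among women recorded as complicated = 0.40 in both arms.
- Mortality among women recorded as not complicated = [0.30(1 − *d*) × 0.40 + 0.70 × 0.1857]/(1 − 0.30*d*).
- Adjusted risk = 0.40*w* + (recorded-none mortality)(1 − *w*), where *w* is the mean recorded prevalence of the two arms.

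**Control *d* = 0.50, intervention *d* = 0.80**
- Recorded-none mortality: control 0.19/0.85 = 0.2235; intervention 0.154/0.76 = 0.2026.
- *w* = (0.15 + 0.24)/2 = 0.195.
- Adjusted risk: control 0.078 + 0.805 × 0.2235 = 0.2579; intervention 0.078 + 0.805 × 0.2026 = 0.2411.
- Risk ratio 0.2411/0.2579 = 0.935, although the true value is 1.

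| Recorded, control v intervention | Adjusted risks | Risk ratio |
|---|---|---|
| 50% v 80% | 25.8% v 24.1% | 0.935 |
| 60% v 80% | 25.5% v 24.4% | 0.955 |
| 50% v 65% | 25.4% v 24.6% | 0.968 |
| equal | 25.0% v 25.0% | 1.000 |

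**Does the known assignment probability protect?** No. With one-to-one allocation the targeting step uses 0.5 for everyone. In the 50% v 80% case the probability of being in the intervention arm is 0.24/(0.15 + 0.24) = 0.62 among women recorded as complicated, and 0.76/(0.85 + 0.76) = 0.47 among the rest. The known value is right marginally but wrong given this covariate. A simulated TMLE with 0.5 fixed (400,000 women, no clustering, 30% complicated, mortality 46.9% v 15.6%) gave 0.903 for 50% v 80%, close to the 0.906 from standardisation with those inputs. With equal 50% recording it gave 0.998.

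**Direction.** Keep the main inputs, set detection at 60% in both arms, and let training cut false positives from 20% to 5%.
- Control: recorded prevalence 0.18 + 0.14 = 0.32; mortality 0.3063 if recorded, 0.2235 if not.
- Intervention: recorded prevalence 0.18 + 0.035 = 0.215; mortality 0.3651 if recorded, 0.2185 if not.
- *w* = 0.2675, so adjusted risks are 24.6% v 25.8% and the risk ratio is 1.05, against the package. With mortality of 46.9% v 15.6% it is 1.07.

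**Sensitivity to the assumptions.** Over a wider assumed grid (20-40% complicated, mortality two to three times higher, 50-70% v 80-90% recorded, no false positives) the risk ratio runs from 0.859 to 0.984. If mortality with a complication is only 30%, the three unequal rows of the table become 0.978, 0.985 and 0.989.

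**The case against.** The strongest reply has four parts.

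- **The list is illustrative.** The method will allow such covariates, and final selection is commonly left to an analysis plan that is not shown. A reader might infer that the primary analysis is committed to this adjustment; the text does not say so. What stands is that the article names this item as baseline information for the primary analysis, and that classification is the problem.
- **Both arms share much of the recording process.** All facilities use the checklist with its risk-factor prompts, and all receive data strengthening and initial checklist instruction. A reader might infer that control staff have nothing directing them to complications, which is wrong. The contrast is PRONTO, QI and extra checklist support on top of a shared instrument. No recording rate by arm is given, so a difference is plausible, not shown.
- **The direction is not fixed.** A reader might infer that the bias must favour the package. That needs training to act mainly by raising detection. If it improves both detection and specificity, the effects can cancel: with the main inputs, detection of 60% v 70% and false positives of 10% v 5% give a risk ratio of 1.003.
- **The size is modest.** At a between-cluster coefficient of variation of 0.2 with 10 facilities of 200 per arm, ignoring matching, the standard error of the log risk ratio is about √[2(0.04 + 0.75/(0.25 × 200))/10] = 0.105. Biases of 0.033 to 0.067 on the log scale are 0.3 to 0.6 of that. Adjusting also for birthweight could shrink them. This is fair, but the bias does not diminish as the sample grows, and a covariate included only for precision does not justify the risk.

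Final newborn diagnosis, in the same list, is also a clearer post-randomisation variable, because it is set after the care under test. That widens the point without removing it.

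**Conclusion.** The concern holds as a risk of bias. The document offers as baseline a covariate that is recorded after randomisation, by unblinded staff, through a process that the package may alter. If recording differs by arm, adjustment can create a mortality difference under no true effect, and the known randomisation probability does not repair it.

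In the main illustration the spurious risk ratio is 0.935 to 0.968, a 3-7% apparent reduction against the 25% reduction that the trial is sized to detect at a coefficient of variation of 0.2. Only the 25% mortality comes from the document. Prevalence, mortality by complication status, recording rates and the absence of false positives are assumptions. The documents do not support a stronger statement that the bias will occur, has a known size or must favour the package. It should be corrected because the item offers only precision and the change is cheap.

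**What to change.** State a rule in Analyses plans: in the primary analysis, individual-level covariates are limited to items whose value and recording the package cannot plausibly affect (for example date of presentation, maternal age and parity/gravidity), together with the facility covariates measured before randomisation.

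Under that rule, remove complications at presentation and final newborn diagnosis. Assess HIV status, last menstrual period and birthweight against the same rule and record the decision for each, so that none is dropped or kept silently. Report recorded complications by arm as a process measure, and use them at most in a sensitivity analysis.

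The cost is a few lines of analysis wording and a possible small loss of precision. Data collection does not change.

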To our knowledge, no published studies have examined the impact of a facility-based intervention package focused on improving uptake of obstetric and neonatal EBPs in order to address preterm mortality. The East Africa Preterm Birth Initiative (PTBi-EA) hypothesizes that a facility-based intervention package administered during the intrapartum and immediate postnatal period will decrease the neonatal mortality rate among preterm neonates. Our package comprises four components: (1) strengthening of routine data collection and data use activities, including regular data quality assessments (DQAs); (2) implementation of the WHO Safe Childbirth Checklist modified for preterm birth; (3) PRONTO provider training and mentoring on key EBPs to strengthen intrapartum and immediate newborn care; and (4) support of QI teams. We believe that these interventions, in combination, will improve awareness and practice of EBPs; teamwork, communication, and respectful maternity care; and use of data for decision-making. We anticipate that results from this study will inform how interventions used in combination can improve personnel and facility capability and readiness to respond to preterm labor and delivery, as well as care for the preterm infant.

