## Discussion

This study focuses on facility-based care of mothers and infants during the intrapartum and immediate newborn period. Across Kenya and Uganda, as well as each of the study facilities, the intervention components will be tailored by in-country stakeholders. For example, the mSCC and PRONTO curriculum will be adapted to ensure adherence to national guidelines. If ongoing QI is already in place at our selected intervention facilities, QI teams and strategies will synergize with these existing efforts or program. This will ensure alignment of the trial to current policies and practices.

The trial, as designed, will assess a package of interventions rather than a single intervention. This approach reflects a consensus in the field that multiple interventions are needed, but creates challenges for researchers accustomed to being able to attribute effects more granularly to specific interventions. We believe that each intervention component reinforces each other to create a synergistic package that, when implemented together, will allow facility providers to improve EBPs and their appropriate documentation (Fig. 3). The interventions target different types of facility staff and cadres of providers, demonstrating that shared and cooperative strategies are needed to address quality of care.

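### The newborn's final diagnosis is listed as a baseline covariate for the primary TMLE, but it follows the care under test, and adjusting for it would remove any effect that acts through it

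*Protocol article*

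**What the plan says.** In the protocol article, Analyses plans, the primary contrast of 28-day mortality uses a hierarchical TMLE: "This will be performed using hierarchical, targeted maximum-likelihood estimation which accounts for within-cluster correlation". Facility-level covariates come first, then individual-level ones: "Additionally, targeted maximum-likelihood estimation will allow us to incorporate individual-level baseline covariate information". The examples start with date of presentation, maternal age, parity or gravidity, HIV status and complications at presentation, and end with "last menstrual period (LMP), infant birthweight, final diagnosis of newborn) in order to improve precision". The targeting step will use the design: "We will directly incorporate knowledge of the pair-matched randomization scheme into estimation".

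The order of events is given elsewhere:

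- Intervention roll-out, Step 2: "Within each matched pair, one facility will be randomized to the intervention arm and the other will be randomized to the control arm". PRONTO and QI are then added at the intervention sites.
- Background, on when the package acts: "a facility-based intervention package administered during the intrapartum and immediate postnatal period will decrease the neonatal mortality rate among preterm neonates".
- PRONTO simulation-based training, on content: "It will include strengthening preterm labor identification with more accurate GA assessments, intrapartum care, and immediate management of fragile infants".
- Outcomes: the comparison of arms is meant to determine the effect of the package, and fresh stillbirths count in the denominator.

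The article does not define the newborn's final diagnosis, does not limit it to conditions present before care, and does not reserve it for a secondary analysis.

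**The concern.** A covariate used for precision in a randomised comparison must be one that the intervention cannot change. The newborn's final diagnosis fails that test. It comes after birth and, at least in part, after the care that PRONTO and QI are meant to improve. The same list restricts maternal and fetal complications to those seen at presentation, but the newborn diagnosis has no such limit.

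If better intrapartum and newborn care prevents some serious diagnoses and so prevents deaths, comparing arms at equal diagnosis discards that benefit. The result is no longer the total effect of the package, which is the trial's stated question. If the diagnosis can code stillbirth or death, the model would adjust in part for the outcome itself.

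Recording is a second route to bias. The trial is unblinded (Intervention roll-out), and facility care providers enter the register data (Data collection/quality control). The Discussion expects the full package to "allow facility providers to improve EBPs and their appropriate documentation". If labels shift in one arm more than the other, the bias could go in either direction.

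**Working it through.** The protocol states no figure on this point, so the check has two parts: the order of events, and an illustration of size.

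**Order of events.** Facilities are randomised; the added components are delivered; a woman presents; intrapartum and immediate newborn care is given; the newborn receives a final diagnosis; 28-day status is determined. Date of presentation, maternal age, parity, HIV status, LMP and complications at presentation are fixed before the care given at that admission. Final diagnosis is not.

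**Inputs from the protocol (Sample size and power calculations).** Control mortality is 25%. The detectable reduction is 25%, giving 25% × 0.75 = 18.75%, a true risk ratio (RR) of 0.75 and a risk difference (RD) of −6.25 points. Cluster size: 46,000 × 0.12 = 5,520; × 0.75 = 4,140; ÷ 20 = 207, consistent with the stated minimum of 200 per facility.

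**Assumed inputs (not in the documents).** A severe final diagnosis occurs in 30% of control infants; mortality is 60% with it and 10% without. This reproduces the planning risk: 0.30 × 0.60 + 0.70 × 0.10 = 0.25.

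**Formulas.** Let s be the share of the effect, on the log scale, that acts through the diagnosis.

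- Mediated part: 0.75^s. Remaining part: 0.75^(1−s).
- Severe diagnosis in the intervention arm: P₁ = (0.25 × 0.75^s − 0.10) / 0.50.
- Pooled prevalence: P = (0.30 + P₁) / 2.
- Standardised control risk: R₀ = 0.10 + 0.50 × P. Standardised intervention risk: R₁ = R₀ × 0.75^(1−s).

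With a saturated outcome model and a known assignment probability of one half, the targeting step leaves this estimate unchanged, so it is the large-sample value for a simple TMLE that includes the diagnosis.

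**Example, s = 0.5.** 0.75^0.5 = 0.866. P₁ = (0.2165 − 0.10) / 0.50 = 0.233. P = 0.2665. R₀ = 0.2333. R₁ = 0.2333 × 0.866 = 0.2020. RR = 0.87, RD = −3.1 points.

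| Share mediated | P₁ | Adjusted RR | Adjusted RD (points) |
|---|---|---|---|
| 0% | 0.300 | 0.75 | −6.25 |
| 25% | 0.265 | 0.81 | −4.7 |
| 50% | 0.233 | 0.87 | −3.1 |
| 75% | 0.203 | 0.93 | −1.6 |
| 100% | 0.175 | 1.00 | 0.0 |

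A simulation of 10 facilities per arm with 200 infants each, a between-facility coefficient of variation of 0.2 and 1,500 replicates agrees. Without the diagnosis, the RD averaged −6.2 to −6.3 points in every scenario. With it, the averages were −6.3, −4.6, −3.1, −1.6 and −0.05. The simulation pools over facilities and is not the full hierarchical estimator.

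**Does the known assignment mechanism help?** No. Randomisation makes assignment independent of covariates that the intervention cannot affect. It gives no such guarantee for a variable that the intervention changes.

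**The case against.** The strongest reply is that the wording is permissive. The text says what TMLE will allow and gives examples; the governing word is baseline, and the final covariate set may be settled in an analysis plan that is not shown. This stands in part: use is foreseen, not fixed. A reader might infer that the primary result will be biased, or that the whole effect will vanish, and the documents support neither. But the protocol expressly names the variable as eligible for the primary estimate and mislabels it, and permissive wording does not cure that.

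Other stronger readings also go too far:

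- *That the diagnosis is known to be a mediator such as asphyxia or infection.* The term is undefined. It could include items that the package cannot change, such as a congenital anomaly. That it can lie on the pathway is an inference from timing.
- *That only one arm is trained to recognise and record complications.* Both arms receive data strengthening and the modified checklist (Trial design), and the conditions that the PRONTO section names are mainly maternal or concern preterm labour. Differential recording is possible, resting on the lack of blinding and the Discussion's expectation about documentation. It is not established.
- *That being recorded after randomisation is itself the fault.* Facilities are randomised first, so every individual-level covariate here is recorded afterwards. The test is whether the care under test can change the variable.

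**Conclusion.** The point holds: the protocol wrongly lists the newborn's final diagnosis as a baseline covariate for the primary analysis. If it were used, the estimate would not be the total effect of the package.

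The size depends on the mediated share, which the documents do not give. Under the stated assumptions there is no attenuation at 0%. At 50% the apparent reduction falls from 25% to about 13%. The effect disappears only at 100%. These figures rest on the protocol's planning values, the assumed diagnosis prevalence and mortality, equal recording in both arms, and no unmeasured common causes of diagnosis and death. If either of the last two fails, the bias could go in either direction, so attenuation is the expected direction and not a certainty. Overlap with the outcome would be worse, but the article does not say whether the diagnosis can code stillbirth or death.

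**What to change.** Delete the newborn's final diagnosis from the covariates named for the primary TMLE. State the rule for the rest: individual-level covariates are limited to those that the care under test cannot change. These are date of presentation, maternal age, parity or gravidity, HIV status, LMP and complications at presentation. Birthweight is measured after delivery, so keep it only on the stated assumption that intrapartum care does not materially alter it. Define final diagnosis, say whether it can code stillbirth or death, and use it only descriptively or in a labelled mediation analysis.

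The cost is a line or two of analysis wording. No data collection or sample size changes. Any precision that the diagnosis would have added is given up, but it could not have been used without risking bias in the primary contrast.
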